### Methods of analysis

The Youth Advisory Board outcome evaluation will include descriptive statistics at the pre- and post-test, to examine changes in patterns of members’ responses, as well as inferential statistics to assess changes over time in outcomes of interest. The meeting notes will be assessed to ensure that key lessons are documented.

## Study phases

### Phase 1: Focus groups to identify multilevel risk and protective factors for nicotine and cannabis vaping

#### Participants

In total, 192 participants (144 youth participants; 48 parent/guardian participants) will participate in one of 24 focus groups (18 youth focus groups; 6 parent/guardian focus groups).

### Inclusion criteria

Focus group participants will be included if they self-identify as American Indian or Alaska Native (AI/AN; alone or in combination with another racial/ethnic group) and live in an Arizona zip code located in an urban area in Flagstaff, Yuma, Tucson, and Phoenix, AZ. Youth will be between the ages of 11 and 17 years old. Adults will be a parent/guardian of an AI/AN child between 11 and 17 years old and have day-to-day responsibility of parenting the child. Youth and adults may be related or unrelated to one another.

### Exclusion criteria

Individuals will be excluded if they are unable or refuse to give informed consent/assent or the youth’s parent/guardian is unable or refuses to give informed parental permission.

### Recruitment strategies

Phoenix Indian Center, with support from Arizona State University, will lead the recruitment efforts drawing on their extensive experience in recruiting participants for research studies, as well as, on their trusted relationships with urban Indigenous families. Recruitment strategies, such as through Phoenix Indian Center’s services, schools, youth centers, health fairs, pow-wows, social media, and word of mouth will be developed and expanded through the Youth Advisory Board.

### Procedures

In order to ensure that diverse adolescent perspectives from across Arizona are represented, youth focus groups will be organized around three categories: (1) non-users – individuals who have never vaped nicotine nor cannabis; (2) contemplators or experimenters – individuals who have tried either nicotine or cannabis vaping or considered trying it, but do not vape nicotine or cannabis regularly; and (3) regular users – individuals who vape either nicotine or cannabis frequently, such as several times per week or daily. In addition, adolescents will also have the option to join the group that aligns best with their sex or gender identity, based on where they feel most comfortable.

Focus groups will occur in-person with 6–8 participants per group, last 90 min, and be audio recorded. Focus groups will be led by two trained facilitators using a semi-structured moderators’ guide that will facilitate discussions, and notes will be taken in order to enhance the accuracy of transcribed data. At the start of each focus group, ground rules will be established to promote a respectful and inclusive environment—at minimum, encouraging participants to speak one at a time, listen actively, and use respectful language to ensure that all voices are heard and valued. Examples of discussion topics include the risks and benefits of nicotine / cannabis vaping, culturally- and community-specific protective factors for nicotine / cannabis vaping, the influence of parents, peers, and teachers on nicotine / cannabis vaping, how neighborhoods impact nicotine / cannabis vaping, the impact of ethnic-racial identity on nicotine / cannabis vaping, and strategies to counter the negative effects of discrimination that help prevent adolescents from nicotine / cannabis vaping.

### Method of analysis

We will use three strategies during the data analysis process to reinforce scientific rigor. First, audio-recordings will be transcribed and verified for accuracy prior to qualitative analysis. All identifying information will be removed. Second, research staff will review focus group recordings on an ongoing basis to identify additional areas of inquiry for subsequent focus groups as needed. Third, we will use data triangulation to compare and identify congruence (or discrepancies) between nicotine and cannabis vaping, as well as between youth and parents (56). Three Indigenous researchers with diverse lived experiences will code and analyze the data.

An inductive thematic analysis approach will be used in three linked, iterative stages: (1) *Data reduction*. De-identified transcripts will be read independently by two coders to identify segments of text that are important or meaningful. The coding process will begin with identifying and categorizing text related to nicotine vaping, including behaviors, risk and protective factors, resistance strategies, and cultural considerations. This same process will then be applied to cannabis vaping, with coders identifying relevant content across the same domains to ensure consistency and comprehensive analysis. Any additional codes will be organized into existing or new categories supported with operational definitions (57). To ensure findings are grounded in the dataset, categories and codes will be compared to original raw data to ensure themes are mutually exclusive, yet broad enough to capture a set of ideas based on direct quotes. Intercoder agreement will be established by two reviewers, and any discrepancies in codes, categories, or definitions will be resolved by a third reviewer to ensure consensus among researchers. (2) *Data display*. We will organize codes into a visual display using the Indigenous Ecological framework to underscore how risky behaviors and environments, as well as resistance strategies and protective factors for vaping among youth are structurally and socially dependent on the places in which they occur (58). We will analyze the findings for areas of convergence between nicotine and cannabis vaping to identify common themes and patterns that can be integrated into the adapted *Living in 2 Worlds* curriculum. In parallel, we will examine points of divergence to determine where distinct aspects of nicotine or cannabis vaping may require separate attention, ensuring that the adaptation includes content specific to each substance where appropriate. The analysis will follow the same approach previously applied to adapt curricula for alcohol, cigarettes, marijuana, and inhalants in *Living in 2 Worlds* (59) and its predecessor, *keepin’ it REAL (kiR)* (60), an evidence-based, universal school-based substance use prevention intervention. (3) *Member Checking*. The codes, categories, and definitions will be reviewed by Phoenix Indian Center staff and the Youth Advisory Board for accuracy.

### Phase 2: Intervention adaptation and pilot test

#### Adaptation

The adaptation process will be guided by the Model for Adaptation Design and Impact, a framework that systematically directs intervention modifications while emphasizing the causal pathways through which adaptation characteristics influence implementation and intervention outcomes (61). This systematic and prospective decision-making approach helps to ensure that adaptations are aligned with the core elements of the intervention, made with a clear goal, and produce positive impacts on implementation and intervention outcomes (61). In collaboration with Phoenix Indian Center and the Youth Advisory Board, the adaptation process will embed multilevel risk and protective factors for nicotine and cannabis vaping in ways that resonate with youth and increase community ownership of *Living in 2 Worlds* (62). Focus group findings will be presented to the research team, Phoenix Indian Center, and the Youth Advisory Board to gather feedback, ideas, and potential adaptations to *Living in 2 Worlds*. We will use various activities (e.g., brainstorming, group discussion) and visual tools (e.g., logic models) to create a roadmap that will inform the adaptations. In addition, we will partner with an Indigenous curriculum designer to ensure Indigenous ways of learning (i.e., circular and wholistic rather than linear and sequential), along with artistic and visual expressions of culture are integrated into *Living in 2 Worlds*. We anticipate adaptations to include adding elements, like examples and activities; substituting elements, like replacing a lesson, activity, or video that addresses nicotine vaping rather than cigarette smoking; and/or deleting elementsno longer temporally appropriate, like “MySpace.” Futhermore, adaptations will also incorporate scenarios that reflect real-life situations in which adolescents encounter risks related to nicotine and cannabis vaping separately, along with effective resistance strategies. These scenarios will be drawn from key themes identified through the focus group analysis. Moreover, some activities may be adapted to specifically address either nicotine or cannabis vaping, depending on the unique focus group findings related to each substance. In addition, given the Phoenix Indian Center’s extensive experience in implementing *Living in 2 Worlds* for the past 13 years, their knowledge and expertise of the pacing of the curriculum, clarity and consistency of materials, usability and alignment of the manual will also be considered during the adaptation process.

### Pilot participants

We will pilot test the adapted version of the *Living in 2 Worlds* intervention in one group of 11 urban Indigenous adolescents recruited through Phoenix Indian Center.

### Inclusion criteria

Youth will be included if they self-identify as American Indian or Alaska Native (AI/AN; alone or in combination with another racial/ethnic group), live in an Arizona zip code located in an urban area of Phoenix, AZ, and are between the ages of 11–14 years old.

### Exclusion criteria

Youth will be excluded if they are unable or refuse to give informed assent or if their parent/guardian is unable or refuses to give informed parental permission.

### Pilot evaluation

The pilot test will serve to gather feedback from youth and the group facilitator around the feasibility, acceptability, appropriateness, of the adaptations. At the conclusion of the pilot implementation, youth will participate in a focus group to gauge if the adapted version of *Living in 2 Worlds* was realistic, believable, fun, provided helpful information on both nicotine and cannabis vaping, and if any changes were needed. The pilot facilitator will provide feedback through an in-depth interview on the strengths and challenges of implementing the intervention components, recommendations for changes to the intervention, and feedback on implementation. We will use questions from the Acceptability of Intervention Measures (AIM), Intervention Appropriateness Measure (IAM), and Feasibility of Intervention Measures (FIM) (63) to guide the in-depth interview. Acceptability will appraise if *Living in 2 Worlds* is enjoyable and satisfactory. Appropriateness will assess the perceived fit of *Living in 2 Worlds*, and feasibility will gauge if *Living in 2 Worlds* can be successfully used and implemented in the schools. These data will be analyzed using the same qualitative methods applied to the Phase 1 focus groups. Findings will be used to inform final adaptations and develop the finalized version of the adapted curriculum.

### Method of analysis

Throughout the entire adaptation process, we will create a matrix of change objectives that will document: (a) what was modified; (b) the type of modification – context or content level; (c) the reasons and rationale for the modification; (d) the outcome, objective, and theoretical foundation targeted by the change, and (e) the data which those changes were derived (64). It is critically important to document the adaptation process, as modifications to evidence-based programs have not been well-documented, understood, or consistently undertaken. Specifying the adaptation processes will support reproducibility and enhance implementation and sustainment (65).

### Phase 3: Randomized controlled trial (RCT) of the vaping adaptation of living in 2 worlds

#### Randomization of schools

Ten middle schools in the Phoenix metropolitan area that have a Native American Education Program will be invited to participate in the study over the course of two cohorts (one cohort per school year). The Native American Education Program is administered by the Office of Indian Education at the Arizona Department of Education with the goal of supporting academic and culture needs of Native American students in Arizona. Schools will be randomly assigned into either: (1) *Living in 2 Worlds* Intervention (5 schools; 180 adolescents; 36 per school) or (2) Comparison group (5 schools; 180 adolescents; 36 per school).

### Inclusion criteria

Participants will be included if they: (a) are an adolescent in 6th – 8th grade (generally 11–14 years old); (b) self-identify as American Indian/Alaska Native alone or in combination with another racial group or a Hispanic ethnic group; and (c) attend one of the urban schools participating in the trial.

### Exclusion criteria

Youth will be excluded if they are unable or refuse to give informed assent or if their parent/guardian is unable or refuses to give informed parental permission.

### Recruitment

Through the auspices of the Native American Education Program, Indigenous students enrolled in the randomized school will be invited to participate in the RCT. A letter will be sent home to obtain parental permission, and the study will be conducted during regular school hours throughout the school year.

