### Intervention group

The *Living in 2 Worlds* intervention groups will be facilitated by Phoenix Indian Center. During the Fall semester, youth will meet at school for 12 weeks, one hour per week, at convenient times (e.g., during lunch period). Urban Indigenous, trained facilitators from Phoenix Indian Center will deliver the *Living in 2 Worlds* curriculum.

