### Comparison group

The comparison group will only complete surveys during the academic year on the same schedule as the *Living in 2 Worlds* intervention group. After RCT data collection is complete, the comparison group will have the opportunity to participate in *Living in 2 Worlds* at no cost during a summer camp implementation to ensure all adolescents have access to the curriculum.

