### Survey data collection

All youth will complete a 30-min self-administered pretest questionnaire, administered electronically via a tablet, one week prior to Living in 2 Worlds beginning (T1 - September), an immediate post-test two months after implementation ends (T2 - January), at a time when the program effects on the prevention of short-term risks for vaping are expected to be strongest, and a follow-up posttest four months later (T3 – May) to assess longer-term efficacy of the intervention at the end of the school year.

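### As worded, pupils are invited and parental permission is sought after their school has been randomised, so the comparability of consenting pupils is at risk if the allocation is known

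*Protocol article*

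**What the plan says.** Everything here is from Phase 3 of the protocol article.

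- **Allocation (Randomization of schools).** "Schools will be randomly assigned into either" the intervention (5 schools, 180 adolescents) or the comparison condition (5 schools, 180 adolescents), at 36 per school, over two yearly cohorts.
- **Invitation (Recruitment).** "Indigenous students enrolled in the randomized school will be invited to participate in the RCT".
- **Consent (Recruitment, Exclusion criteria).** "A letter will be sent home to obtain parental permission". Assent is also needed: "Youth will be excluded if they are unable or refuse to give informed assent". Refusal of parental permission excludes as well.
- **What joining means in an intervention school (Intervention group).** "youth will meet at school for 12 weeks, one hour per week, at convenient times (e.g., during lunch period".
- **What joining means in a comparison school (Comparison group).** "The comparison group will only complete surveys during the academic year", with a free summer-camp version offered once data collection is complete.
- **Baseline (Survey data collection).** T1 is taken in September, "one week prior to Living in 2 Worlds beginning".
- **Analysis (Statistical data analysis plans).** Intent-to-treat models of change across T1, T2 and T3, with control for school and for those demographic characteristics found not to be equivalent at baseline.

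**The concern.** In a cluster trial, randomisation makes the schools comparable, and through them the full set of eligible pupils. It does not by itself make the pupils who consent comparable. That holds only if the decision to join cannot depend on the arm, which is safest when consent precedes disclosure of the allocation. The Recruitment wording puts the steps in the other order.

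The two offers differ enough for this to matter. A weekly cultural programme, possibly at lunch, may attract or deter different families than three surveys would. The article itself expects the programme to have more impact on youth who feel close to American Indian cultural foundations (Quantitative hypotheses). Cultural connection could therefore influence who agrees to join, and it is also one of the study's outcomes (Skills acquired in *Living in 2 Worlds*).

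A second consequence follows if the arm is known by T1. Baseline vaping is self-reported, and the T1 answers identify who has not yet vaped, which is the group at risk for the initiation hypothesis. Reporting that differed by arm would enter that definition directly.

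Neither problem can be repaired once enrolment has closed.

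**Working it through.** **1. Order of events.** Allocation is of schools. The Recruitment sentence describes the school as already randomised when its pupils are invited, and the letter for parental permission follows in the same paragraph. T1 comes one week before the first lesson, so after consent. No other section reverses this order. No dates are given for allocation, invitation or disclosure, so the order rests on that sentence.

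**2. What the planned analysis can absorb.**
- Intent-to-treat keeps every enrolled pupil in the allocated arm. Selection at consent happens before a pupil enters that set, so intent-to-treat does not act on it.
- The change models use T1 values. Baseline vaping and cultural connection are both in the study's measures, so imbalance in them can be absorbed as far as they are measured well.
- The demographic covariates (for example sex, age, school grades, household type, free lunch) enter only where baseline equivalence fails.
- Motivation, family attitudes and willingness to attend a programme are not among the listed covariates.

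**3. The plan's own sample-size figures, as a check.** Inputs from Sample size calculations: d = 0.31, power 0.80, α = 0.05 (two-sided assumed), pretest R² = 0.67, attrition 20%.
- n per arm = 2 × (1.96 + 0.84)² × (1 − 0.67) / 0.31² = 54, so 108 in total. 108 / 0.80 = 135, against the stated 132 (within 3%).
- With d = 0.19 the same formula gives 144 per arm, 288 in total, and 288 / 0.80 = 360, which matches the stated 360.

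The point disputes neither figure. The 144 analysed per arm is carried into step 4.

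**4. Sensitivity to a residual imbalance (assumed values).** With no true effect and clustering ignored, SE = √(0.33 × 2/144) = 0.068 SD. If an imbalance b remains after adjustment, the two-sided rejection rate is 1 − Φ(1.96 − b/SE) + Φ(−1.96 − b/SE):

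| b (SD) | b / 0.31 | Rejection rate at nominal 0.05 |
|---|---|---|
| 0 | 0 | 0.05 |
| 0.05 | 0.16 | 0.11 |
| 0.10 | 0.32 | 0.31 |
| 0.15 | 0.48 | 0.60 |

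Allowing for clustering would enlarge the SE and so reduce these rates for a given b. The table shows sensitivity; it is not evidence that any b exists.

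**5. How differential consent creates imbalance (assumed values).** Suppose 30% of pupils are high-risk, outcome risk is 40% in them and 10% in the others, and consent is 60% throughout. The outcome rate is 0.30 × 40% + 0.70 × 10% = 19.0%. If high-risk pupils consent at only 40% in one arm, their share there is (0.30 × 0.40) / (0.30 × 0.40 + 0.70 × 0.60) = 22.2%, and the rate becomes 0.222 × 40% + 0.778 × 10% = 16.7% with no intervention effect. Consent of 50% or 30% gives 17.9% or 15.3%. These are raw rates; T1 adjustment would remove whatever part the T1 measures capture.

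**The case against.** The strongest reply is that the order hangs on one word in a condensed article. The inclusion criteria speak only of schools taking part in the trial, and the Recruitment sentence may simply mean a trial school. The full protocol may put consent first. This is a fair limit on certainty. It does not remove the point, because the sentence as written states the opposite and nothing else corrects it.

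A reader might infer that families know their arm when they consent and when they answer T1. The article does not say so. It describes what each arm receives, not what the letter tells families, and an arm-neutral letter would be compatible with the text. The concern is therefore conditional on disclosure.

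The arms also differ less than they first appear to: comparison pupils are offered the programme free afterwards, and the survey incentives are not said to differ by arm. This weakens the motive for differential consent without removing it.

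A reader might also be tempted to size the bias from assumed vaping rates. Enrolled 30-day vaping of 10% versus 15% gives OR = (0.15/0.85)/(0.10/0.90) = 1.59 and d = ln(1.59) × √3/π = 0.26, seemingly close to the planned 0.31. That comparison is not supported. The rates are invented, and the 0.26 is a raw baseline gap rather than bias in the effect estimate. If the gap is stable, a change score cancels it. Linear pretest adjustment with r = √0.67 = 0.82 leaves about 0.255 × 0.18 = 0.046, or 15% of 0.31.

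**Conclusion.** The point holds as a conditional design risk that should be dealt with before Phase 3 enrolment. As worded, invitation and permission follow randomisation of the school, and the arms offer different things. If families or recruiters know the allocation, consent can differ by arm, and T1 self-reports may be affected too.

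It would go too far to infer that the trial loses the protection of randomisation. Schools remain randomised; what is at risk is the comparability of the pupils who consent, and bias is possible rather than certain.

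Its size cannot be computed, since the article gives no consent rates by school or arm. The illustrations show only that a modest imbalance surviving adjustment would matter at this sample size. They rest on assumed inputs, and the error rates ignore clustering.

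**What to change.** **Preferred.** Within each cohort, complete parental permission, assent and the T1 survey in all schools before allocation is disclosed to schools, families and recruiting staff. Use one identical letter describing both arms. Because T1 already falls one week before the first lesson, disclosure can follow T1 on the existing calendar.

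**If full sequencing is not workable.** Have the identical, arm-neutral letter sent by staff unaware of allocation. Report the numbers eligible, invited and consented by school and arm. Adjust for T1 vaping and its risk factors in all models, rather than only for demographics found to differ.

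**If consent already precedes disclosure.** Correct the Recruitment sentence to say so.

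**Cost.** A change of sequence and one letter, with no added measurements. The real downside is shorter notice for schools and facilitators, who must fit sessions into the school day. The article does not show whether one week is enough, so this should be checked with the schools and the community partner.
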